### Sampling procedure

For the quantitative component of the study described in this protocol, a cluster will be composed of the nurses and patients of a HD department. The HD units of every hospital in French Switzerland will be contacted to take part in the study, for a total of 13 units. To date, 10 units have already expressed their desire to take part in the study: Centre Hospitalier Universitaire Vaudois (Lausanne), Ensemble Hospitalier de la Côte (Morge), Établissements Hospitaliers du Nord Vaudois (Yverdon), Hôpital du Valais (three independent sites in Sion, Sierre, and Martigny), Hôpital du Jura (Delémont and Porrentruy), Hôpital Intercantonal de la Broye (Payerne), Hôpital Riviera-Chablais (Monthey), Hôpitaux Universitaires de Genève (Geneva).

Once the HD units and all the nurses and patients that compose them are enrolled, they will be randomised by computer to the EG or the WLCG. Among the 1024 (=2^10^) possible allocations to EG and WLCG, we will limit our choices to those where both the EG and the WLCG contain at least 50 nurses. Under this constraint, there are still 410 possible allocations and the number of units per group ranges from 2 to 8. The R software (version 3.3.0) [36] will be used to choose an allocation at random from among these 410 possibilities. All units will have the same probability of being included in the EG.

For the qualitative component, a purposive sample will be used. This sampling method allows selecting persons that have lived the experience under study (in our case, participation in the EI) and that agree to share it. It is best with this method to recruit a wide variety of participants in order to collect as diverse a set of viewpoints as possible on the phenomenon under study. Participants for this component will be selected from among the EG nurses. Moreover, in order to take account of staff heterogeneity across EG units, the number of participants invited to be interviewed will be weighted based on unit size. It is difficult with qualitative approaches to determine beforehand the number of participants required. Benner [37] recommends 5 to 25 but specifies that it is necessary to keep interviewing until the discourse becomes redundant, that is, until adding participants to the sample and more data to those already collected sheds no more light on the phenomenon under study [38]. Based on the experience of researchers in the field, it is estimated that a sample of 18 participants will be required.

### Intervention description and delivery

The EI was originally developed with rehabilitation nurses working with spinal cord injury patients by Quebec researchers [19, 35] guided by Watson’s Theory of Human Caring [20, 21, 31]. The researchers, experts in humanist philosophy, focused on the choice and definition of the theoretical concepts to be taught and on the creation of learning activities [19] (see Table 1) deemed indispensable for optimal concept appropriation and application within the clinical care context of spinal cord injury rehabilitation (Quebec) and, later, haemodialysis (Switzerland). In Switzerland, the EI will be delivered by the two principal researchers of the study described in this protocol. Each has substantial clinical experience with persons living with a chronic condition and has previously taught Watson’s Theory of Human Caring [20, 21]. The EI will be delivered to all the nurses participating in the study but at different times depending on group assignment (see Table 2). Intervention delivery schedules will be specific to each centre based on availability within work schedules. In order to facilitate learning and interactions during sessions, groups will comprise 3 to 8 people. Each group will complete all four sessions, each lasting 3.5 h. There will be a minimum interval of one week between sessions to afford participants the necessary time to reflect on the content, to appropriate it and to apply it in their clinical practice. The intervention will be implemented in the training rooms of the establishments partnering in the research project.

**Table 1 Tab1:** Processes and content of educational intervention

Session and topic	Objectives	Learning activities
Session #1: Acquisition of core concepts of caring practice	- Caring values, attitudes and behaviours - Describe core concepts of Watson’s Theory of Human Caring ▪ Phenomenal field ▪ Transpersonal caring relationship ▪ Caring occasion and caring moment ▪ Moral ideal - Develop concept of “phenomenal field” further - Recognise concepts taught in caring reflective clinical vignette #1 - Gain awareness of relevance of humanistic approach to caring for HD patients - Present a schematic representation of theoretical concepts	- Print documents and PowerPoint presentation - Print article on theory [38] - Focusing exercise - Theory course - Practical listening exercise - Narrative #1: Roger on concept of phenomenal field - Plenary discussion - Schematisation of theoretical concepts [57] - Reflective assignments (1) Read caring reflective clinical vignette #1: The caring moment: a moment of well-being for both patient and nurse (2) Answer reflective questions
Session #2: Acquisition of coreconcepts of caring practice	- Describe concept of Watson’s 10 carative factors and give clinical example for each - Integrate concept of 10 carative factors further - Recognise concepts taught in caring reflective clinical vignette #2 - Present a schematic representation of theoretical concepts	- Print documents and PowerPoint presentation - Review of session #1 (content and clinical vignette) and questions - Focusing exercise - Narrative #2: Roger on changing phenomenal field and carative factors - Theory course - Exercise on identifying nurse and patient resources [58, 59] - Group discussion - Schematisation of theoretical concepts [57] - Reflective assignments (1) Read caring reflective clinical vignette #2: Nursing interventions guided by carative factors to comfort Simone (2) Answer reflective questions (3) Propose resource exercise to a HD patient and do a summary
Session #3: Appropriation of concept of hope Incorporation of all concepts taught	- Describe different attributes of concept of hope - Gain awareness of what hope can contribute to HD patient QoL - Recognise different humanistic interventions that influence hope in caring reflective clinical vignette #3 - Discuss search for meaning in HD patients - Present schematic representation of theoretical concepts	- Print documents and PowerPoint presentation - Review of session #2 (content, clinical vignette and exercise to identify resources with a patient) and questions - Focusing exercise - Narrative #3: Roger on changing phenomenal field and nursing interventions to strengthen hope - Theory Course - Group discussion - Schematisation of theoretical concepts [57]. - Reflective assignments (1) Read: Caring reflective clinical vignette #3: Inspiring hope like a breath of life (2) Answer reflective questions
Session #4: Enactment of different caring attitudes and behaviours in an intermediary simulation exercise with professional actor	- Mobilise concepts of Watson’s Theory of Human Caring in a safe environment where mistakes are permitted (simulations) - Foster connections between knowledge acquired and HD clinical practice	- Print documents - Review of session #3 (content and clinical vignette) and questions - Two simulation exercises comprising: *briefing:* reading of first clinical situation and choice of nurse for simulated practice; *simulated practice:* simulation with nurse and actor according to predetermined scenario for actor; *debriefing:* sharing of experiences (nurse, actor and group); remobilisation, deeper understanding and further development of theoretical concepts

**Table 2 Tab2:** Data collection over time for nurses and patients

		Enrolment	Allocation	Post-allocation				Close-out	Post-trial
TIME POINT		t-_1_	t_0_	Intervention	t_1_ immediately post-intervention	t_2_ 2 months post-intervention	t_3_ 6 months post-intervention	t_4_ 12 months post-intervention	Intervention
ENROLMENT	Project presentation to nursing care directors at different sites	x							
	HD units recruited	x							
	Informed consent obtained for HD nurses and patients		x						
	Cluster randomisation		x						
INTERVENTION	Experimental group (EG)			➨					
	Waiting-list control group (WLCG)								➨
ASSESSMENT									
HD nurses (EG and WLCG)	QUANTITATIVE DATA								
	Sociodemographic questionnaire		x						
	CNPI-70/EIIP-70		x		x		x	x	
	GEQ		x		x		x	x	
	QoWL		x		x		x	x	
	Team cohesion		x		x		x	x	
HD nurses (EG)	QUALITATIVE DATA								
	Qualitative interviews					x			
HD patients (EG and WLCG)	Sociodemographic and medical questionnaire		x						
	CNPI-70/EIIP-70		x		x		x	x	
	WHOQOL-BREF		x		x		x	x	

### Quantitative data collection

Various instruments will be used to collect data from participating HD nurses and patients.

### HD nurses

#### Sociodemographic data

At pre-test (T0), personal data (sex, age) and work-related information (employment status, years of experience as HD nurse, number of patients attended to per work shift) will be collected.

The nurse-patient relationship (NPR) will be measured with the French-language version (EIIP-70) [39] of the Caring Nurse-Patient Interaction Scale (CNPI-70). This tool comprises 70 items covering 10 dimensions that capture each of Watson’s 10 CF. It allows nurses to self-rate their frequency of caring attitudes/behaviours. The dimensions covered by the instrument are the following [39]: humanism (6 items), hope (7 items), sensitivity (6 items), relationship (7 items), emotions (6 items), problem solving (6 items), teaching (11 items), assistance (10 items), and existential factors (6 items). Respondents must choose from five responses ranging from 1 (almost never) to 5 (almost always). This tool was validated on 377 nursing students and demonstrated good psychometric properties (range of Cronbach’s alphas for the 10 sub-dimensions of 0.73 to 0.91) [39]. Moreover, the two pilot studies showed respondents had no difficulty understanding the questionnaire and completing all the questions.

Team cohesion will be measured with the Group Environment Questionnaire (GEQ) [40] adapted for work teams [41]. A French-language version of the questionnaire was created following the back-translation procedure [41]. Like the original, the French-language version comprises 18 items and encompasses the four dimensions of team cohesion [42], namely, respondent social-related attraction to group (five items, one of which is reverse scored), respondent task-related attraction to group (four items, two of which are reverse scored), social-related group integration as perceived by respondent (four items, two of which are reverse scored), and task-related group integration as perceived by respondent (five items, one of which is reverse scored). The response scale ranges from 1 (strongly disagree) to 5 (strongly agree). The questionnaire was tested on a sample of nurses from another healthcare institution. No major comprehension difficulties emerged. Cronbach’s alphas for the different dimensions ran from 0.71 to 0.81 [41].

Quality of working life (QoWL) will be measured with a scale developed by Elizur and Shye [43], translated into French and validated by Delmas, Escobar, and Duquette [44]. The scale is composed of 16 items exploring four dimensions of QoWL [43]: psychological (items 1–4), physical (items 5–8), social (items 9–12), and cultural (items 13–16). Respondents must choose from six answers on a Likert scale ranging from “a very large part” to “very little”. The scale’s empirical structure was tested on a population of 540 Hungarian industrial workers [43]. The internal consistency of the overall scale was estimated at 0.90 (Cronbach’s alpha). Also, Delmas, Escobar, and Duquette [44] obtained Cronbach’s alphas of 0.87 to 0.89 for its various dimensions with a population of French nurses.

### HD patients

The patients will complete a sociodemographic and medical questionnaire. It will be based on elements selected by Boini et al. [45] for the purposes of a longitudinal study of the QoL of 1000 French chronic kidney disease patients. It will comprise several sections covering sociodemographic characteristics (age, sex, marital status, number of children, income), clinical status, and bio-clinical data (weight, size, number of drugs taken daily, alcohol and tobacco use, albuminemia level, haemoglobin level), comorbidity (cardiovascular disease, diabetes, hypertension), and disabilities (amputation of lower limbs, para/hemiplegia, blindness). This questionnaire presented no particular problems when previously tested on Swiss HD patients [6, 46].

The nurse-patient relationship (NPR) will be explored with the French-language version (EIIP-70) [3] of the CNPI-70 (for a description, see *Nurse* section above). The items were adapted to the patient’s viewpoint merely by changing the person addressed. The scale presented perfectly satisfactory psychometric properties (Cronbach’s alphas of 0.75 to 0.85) when validated on a French population of patients living with HIV [47]. The scale allows HD patients to assess nurse caring attitudes and behaviours.

Quality of life (QoL) of HD patients will be explored with the WHOQOL-BREF. This scale is a generic instrument that serves to explore perceived QoL [48] and impact of health problems on QoL [49]. It comprises 26 items exploring four dimensions: physical health (7 items), psychological health (6 items), social relationships (3 items), and environment (8 items). It also contains two items measuring overall QoL, which is an added advantage of this instrument. Respondents must choose from five responses on a Likert scale of 0 (not at all) to 5 (completely). The WHOQOL-BREF yields an overall “QoL profile” score ranging from 0 to 100, as well as scores for each dimension. A high score indicates a high perceived QoL [48, 49]. The English-language version of the instrument has shown good content and discriminant validity, as well as excellent internal consistency [48]. The French-language version translated and validated by Leplège et al. [50] has shown perfectly satisfactory psychometric properties (Cronbach’s alphas of 0.82, 0.81, 0.68, and 0.80, respectively, for the above dimensions) and good acceptability by the population, with a non-response rate below 5%. When the questionnaire was administered in the pilot study [35] conducted in Switzerland, HD patients had no difficulty completing the questionnaire.

### Qualitative data collection

Qualitative data will be collected through a phenomenological method, the Relational Caring Inquiry, developed by Cara [51, 52] on the grounds of Watson’s work and humanist philosophy. The method entails seven inter-related dynamic phases: 1) acknowledging researcher’s worldview; 2) seeking participants; 3) being present for participants’ stories; 4) discovering essence of participants’ stories; 5) reciprocating participants’ stories; 6) relational caring process; and 7) elucidating essence of phenomenon [53]. An interview guide has been developed by the investigators to enhance the rigour of qualitative data collection. The aim of the phenomenological qualitative approach used is to gain a deeper understanding and description of nurse perceptions regarding: 1) post-intervention practice transformation; 2) post-intervention teamwork cohesion transformation; and 3) intervention benefits for themselves and HD patients. Data will be collected by way of semi-structured interviews recorded at the EG nurses’ workplace, in a place providing privacy, where a relationship of mutual trust can be cultivated and confidentiality ensured. Finally, to ensure the rigour of the qualitative data collection process, the investigators will keep a logbook for tracking purposes, in which they will jot down methodological notes (e.g., events in development/evolution of method, changes), theoretical notes (e.g., interpretations, deductions, hypotheses, theoretical knowledge), and personal notes (e.g., feelings, emotions, impressions).

### Data analysis

For the quantitative component of the study described in this protocol, first, we will check the data for inclusion conditions and outliers. Outlying data will be verified individually. Second, associations between factors and outcomes will be described using frequencies, means and standard deviations or medians and interquartile ranges. In addition, these associations will be evaluated using chi-square tests, Fisher tests or analyses of variance. Third, linear regression models adjusted for significant sociodemographic and health variables will be used to examine the intervention’s effect on the different variables selected for the study, keeping in mind that nurse QoWL remains the key outcome variable. Moreover, we will consider a random intercept to take HD unit variance into account. Fourth, we will test whether team cohesion acts as a mediator in the relationship between NPR (independent variable) and nurse QoWL (outcome variable). For this purpose, we will run three regressions: 1) regression of mediator on independent variable (EIIP-70); 2) regression of outcome variable (QoWL) on independent variable; and 3) regression of outcome variable on both independent variable and mediator. Fifth, an intention-to-treat analysis will be conducted of the data on all participants, whether they complete the intervention or not. This will diminish bias related to protocol deviations or withdrawals and will allow estimating the intervention’s effects under conditions that are close to real life. Sixth, based on sample size and sample design (10 HD units of different sizes for a total of 135 nurses) and considering an intra-class correlation coefficient of 0.03 for the HD units, we will be able to detect an effect size of 0.6, with statistical power of 0.8 and significance level at 0.05 for all analyses. The expected effect size has been fixed by the investigators and corresponds to the minimal clinically significant effect. The intra-class correlation coefficient selected is in line with Giraudeau’s recommendations [52] of 0.001 to 0.05 for a cluster RCT. The data will be analysed using the R software [54].

The qualitative data will be organised using NVivo software (version 11). All of the interviews will be transcribed verbatim. Following the RCI phenomenological method [51, 52], transcripts will be analysed to identify units of meaning (first-level reflection), that is, ideas specifically regarding the phenomenon under study. Next, the units will be grouped into sub-themes (second-level reflection), which correspond to descriptive elements that reflect as best possible the participants’ transcripts. Then, the sub-themes will be organised into themes (third-level reflection) based on a convergence of ideas [52]. Thereafter, an in-depth analysis of these themes, as well as use of free imaginary variation, will allow us to identify the essential constructs of the phenomenon, that is, the eidos-themes (fourth-level reflection) [52]. Finally, these eidos-themes will allow the universal essence of the phenomenon under study to emerge (fifth-level reflection) [51, 52]. The scientific validity standards that apply to qualitative research, namely, authenticity (confirmability), credibility, criticality (dependability), integrity and transferability (fittingness) [55], will be a constant consideration for the researchers.

Convergence between the quantitative and qualitative results will then be analysed by comparing and discussing the two using a side-by-side approach [33, 56]. The aim here will be to determine the extent to which the results derived from the two types of data converge.

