**Methods/design:**

The study described in this protocol will use a mixed-method cluster randomised controlled trial design. For the quantitative component, nurse and patient data will be collected through questionnaires. The accessible population of 135 nurses and 430 patients will be clustered into 10 HD units. These units will be randomised into an experimental group (EG) and a waiting-list control group (WLCG). Measurements will be taken at baseline (pre-intervention) and repeatedly over time (post-intervention): immediately at EI completion and six and 12 months thereafter. For the qualitative portion of the study, 18 semi-structured interviews will be conducted with EG nurses picked at random two months after EI completion to explore perceived changes in nurse humanistic practice. Qualitative data will be analysed through the relational caring inquiry method, a phenomenological approach. Descriptive and inferential statistics will be computed from the quantitative data.

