### Theoretical framework

In order to enhance the validity of the research through the judicious choice of a theoretical framework [28] to orient the selection of the variables to explore, we propose grounding the study described in this protocol in Duffy and Hoskins’ Quality-Caring Model [9], a middle-range theory that serves to understand the NPR as theorised on the basis of Watson’s 10 carative factors (CF) [20, 21] and to interpret the emergence of positive outcomes for patients, families, health professionals and, more broadly, the healthcare system [29]. According to this model, the NPR is therapeutic for patients by helping raise their QoL and their satisfaction with care. Thus, quality of NPR is a major factor in patient health and an indicator of care quality and patient safety [9]. According to Donabedian’s quality paradigm [30], Duffy and Hoskins’ model [9, 29] can be broken down into three parts: structure, process and outcome. **Structure** includes all factors related to nurses, patients and the healthcare system upstream from care delivery. Where nurses are concerned, these encompass sociodemographic characteristics (e.g., age, years of experience, educational level, shift) and workload-related variables (e.g., patient-nurse ratio, overtime hours worked, team cohesion). For the purpose of our study, we will measure nurse-perceived quality of NPR and QoWL prior to the intervention. As for the patients, we will document sociodemographic characteristics, severity of illness, and comorbidity. We will also measure patient-perceived quality of NPR and QoL. These variables are compatible with the elements that compose Duffy and Hoskins’ model [9, 29]. The measures taken prior to the intervention (pre-test) will provide baseline values. **Process** [9, 29] refers to nurse clinical practice, especially in connection with the caring relationship that nurses cultivate with care recipients. The caring relationship is at the heart of the process and reflects nurse commitment to caring for patients. It is in this light that the relevance of delivering an EI based on the concepts of Watson’s theory [20, 31] becomes clear, given that the intervention is intended to mobilise and consolidate nurse abilities to dispense care according to the caring approach. This is all the more important in HD units where nursing practice revolves around tech-heavy tasks [24]. **Outcome**, the last component of the theory, comprises two levels: intermediate and terminal. For Duffy and Hoskins [9, 29], **intermediate outcomes** correspond to changes in attitudes/behaviours among carers, patients or an organisation, which lead to changes in the orientation of the clinical follow-up of patients. In our study, the following intermediate outcomes will be examined: 1) nurse-perceived changes in caring attitudes/behaviours and patient-perceived changes in nurse caring attitudes/behaviours post-intervention; 2) nurse-perceived changes in team cohesion post-intervention; and 3) quality of NPR. To this end, nurses and patients will complete measures of quality of NPR post-intervention. Moreover, phenomenological qualitative interviews will be conducted with nurses to obtain additional information on their perception of change in quality of NPR post-intervention. Finally, **terminal outcomes** are tied to the major concepts that can affect the future of both HD patients and nurses. In our study, patient QoL and nurse QoWL will be the primary outcomes of the study. In sum, the Quality-Caring Model [9, 29] will provide a solid theoretical structure for examining the effects of the intervention on both the nurses and the patients participating in the research.

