#### Primary objectives

1) Describe levels of the variables of interest among nurses (quality of NPR, team cohesion, QoWL) and patients (quality of NPR, QoL) pre-intervention (T0); and 2) examine the effects of the intervention on the variables of interest among participating nurses and patients immediately post-intervention (T1) and twice more over time (T3 and T4).

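### The effect model gives the T0 outcome score no stated place and chooses its covariates by significance, which costs precision the trial could have for free

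*Protocol article*

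**What the plan says.** The Data analysis section of the protocol article sets out the quantitative steps in order. Associations between factors and outcomes come first, and "these associations will be evaluated using chi-square tests, Fisher tests or analyses of variance". The effect model follows: "linear regression models adjusted for significant sociodemographic and health variables will be used to examine" the effect of the intervention, with the reminder that "nurse QoWL remains the key outcome variable". On clustering, the article says "we will consider a random intercept to take HD unit variance into account". No person-level effect is mentioned.

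Table 2 schedules the outcome instruments for nurses and patients, in both groups, at T0, T1, T3 and T4. The article gives the T0 scores two uses. The first primary objective is to describe pre-intervention levels, and the Theoretical framework section states that "The measures taken prior to the intervention (pre-test) will provide baseline values". The five hypotheses are all worded as differences between the groups after the intervention.

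The power statement rests on "10 HD units of different sizes for a total of 135 nurses", an ICC of 0.03, an effect size of 0.6, power 0.8 and significance level 0.05. It mentions no baseline adjustment. The Preliminary results section reports a first wave of 100 nurses and 140 patients.

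**The concern.** Two features of the stated model are weak.

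- **T0 is not used.** A participant's own earlier score on the same scale is normally the strongest predictor of the later score. It is neither a sociodemographic nor a health variable in the lists the article gives, and it does not enter as a change score or as a repeated measure with a person-level effect. The variance it could explain stays in the residual.
- **Covariates are chosen by significance.** The adjustment set then depends on the outcome data. It can change between outcomes and visits, so effects at T1, T3 and T4 may be adjusted for different things.

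This matters more with 10 unequal units. The Sampling procedure section allows 2 to 8 units per arm and constrains only the number of nurses per arm, so the design does nothing to balance T0 scores.

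**Working it through.** **Inputs from the article:** 135 nurses in 10 units (mean 13.5), ICC 0.03, effect 0.6 SD, alpha 0.05, at least 50 nurses per arm, first wave of 100 nurses. **Assumed:** two-sided testing, the spread of unit sizes (CV), and r, the T0/follow-up correlation.

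**1. The article's own figure.** Design effect DE = 1 + ((1 + CV²) × 13.5 − 1) × 0.03; SE = √(DE × (1/n₁ + 1/n₂)); power = Φ(0.6/SE − 1.96).

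| Split | CV | DE | Power |
|---|---|---|---|
| 67.5/67.5 | 0 | 1.375 | 0.844 |
| 50/85 | 0 | 1.375 | 0.819 |
| 50/85 | 0.4 | 1.440 | 0.801 |
| 67.5/67.5 | 0.65 | 1.546 | 0.800 |

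The stated 0.80 is reproduced without any baseline adjustment once unequal units or the allowed imbalance is included.

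**2. Adding T0, 135 nurses.** Take the last row: SE = √(1.546 × 2/67.5) = 0.214. With T0 as a covariate the variance is multiplied by 1 − r². In the cautious version T0 explains only within-unit variance, so DE becomes 0.97 × (1 − r²) + (1.546 − 0.97).

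| r | 1 − r² | Detectable effect | Power, normal | Power, within-unit only | Power, t on 8 df |
|---|---|---|---|---|---|
| no T0 | 1 | 0.60 | 0.80 | 0.80 | 0.69 |
| 0.3 | 0.91 | 0.57 | 0.84 | 0.82 | 0.73 |
| 0.5 | 0.75 | 0.52 | 0.90 | 0.86 | 0.81 |
| 0.7 | 0.51 | 0.43 | 0.975 | 0.92 | 0.93 |

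The last column uses the full 1 − r² reduction.

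**3. Adding T0, 100 nurses.** Assumed unit sizes 22, 18, 12, 10, 9, 8, 7, 6, 5 and 3 (sum 100), ICC 0.03, critical value t = 2.306 on 8 df. A random-intercept simulation without T0 gives a mean SE of 0.239. The formula in step 1, with mean size 10 and CV 0.56, gives DE 1.365 and, for 50/50, √(1.365 × 0.04) = 0.234, which agrees. Scaling 0.239 by √(1 − r²) and using the noncentral t:

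| r | SE | Power for 0.6 SD |
|---|---|---|
| no T0 | 0.239 | 60% |
| 0.3 | 0.228 | 64% |
| 0.5 | 0.207 | 72% |
| 0.6 | 0.191 | 78% |
| 0.7 | 0.171 | 87% |

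A separate simulation with random allocation under a scaled minimum-nurse rule gave about 60% without T0, and 64%, 72–74%, 77–81% and 84–89% with it at the same values of r. If T0 explains only within-unit variance, r = 0.6 gives an SE of about 0.20 and power of about 75%.

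**4. Chance T0 imbalance in the same setting.** The T0 difference between arms has the same SE, 0.239. Its mean absolute size is 0.239 × √(2/π) = 0.19 SD, and about one allocation in five exceeds 0.3 SD. An unadjusted model passes a fraction r of the realised difference into the estimate.

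**5. The selection rule.** The HD patients section lists 18 candidate variables, counting alcohol and tobacco separately. At the 5% level (assumed), 18 × 0.05 = 0.9 would be selected by chance in each screen if none mattered. Three nurse and two patient outcomes at three follow-ups allow up to 5 × 3 = 15 separately chosen sets.

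**The case against.** The strongest reply is that leaving out T0 is inferred. The article never says what the dependent variable is. A change score or a repeated-measures model would use T0 without naming it as a covariate, and the abstract does describe measurement at baseline and repeatedly afterwards. A condensed article may leave model form to a fuller document. This stands in part: a reader might infer that the plan rules T0 out, and it does not. But the article goes beyond silence. It names a class of covariates and a rule for choosing them; T0 is outside that class, and no other route for it is given. The selection rule itself is stated outright.

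Three stronger readings also fail.

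- **Bias.** A reader might infer that T0 differences between arms bias the result. Allocation is random, so chance imbalance is sampling variance already reflected in the standard error. The loss is efficiency.
- **A wrong sample size.** A reader might infer that the power statement is in error because T0 is absent. It was made without baseline adjustment and reproduces. The lower figures above come from 100 nurses and an 8-df reference, which are separate matters.
- **One large gain.** A reader might fix on a single big rise in power. The gain depends on r, which is unknown, and is modest at r = 0.3.

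How far the selection rule would move the effect estimate has not been quantified here. That data entry and analysis are done by a group not involved in the intervention is a partial safeguard, but the covariate set remains data-dependent.

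**Conclusion.** The point holds as a loss of precision and an avoidable data-dependence in the effect model, including the model for nurse QoWL, the key outcome. On the article's 135 nurses, with the normal approximation and a unit-size CV of 0.65, the detectable effect falls from 0.60 to between 0.57 (r = 0.3) and 0.43 (r = 0.7) when T0 is added. On 100 nurses with a t reference the gain is between 4 percentage points (r = 0.3) and 27 (r = 0.7). The gains are somewhat smaller if T0 explains only within-unit variance. Both ranges rest on assumed r and assumed unit sizes; the direction does not. The validity of the randomised comparison is not in question. The change is worth making because it costs almost nothing.

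**What to change.** In the Data analysis section, replace the covariate clause with: *adjusted for the T0 value of the same outcome and a short covariate list fixed before outcome data are analysed and kept the same for all outcomes and time points within each population (nurses, patients), whether or not significant.* The investigators should choose the other covariates on subject-matter grounds; the article gives no figures that would favour particular ones. Add one sentence with a simple rule for participants whose T0 score is missing. If a change-score or repeated-measures model was intended, say so, and state how T0 enters it.

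The cost is one or two sentences. The T0 measurements are already scheduled in both arms, so no new data collection is needed, and the design and stated sample size stay as they are.
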